##### Economics

The Sustainable East Africa Research on Community Health (SEARCH) economic assessment is a standardized questionnaire developed by [name] for use with HIV-affected populations in sub-Saharan Africa. The instrument assesses both formal (e.g., salaries, wages) and informal (e.g., crops, animals) income in order to accurately capture economic activity in the target population.

### Sample size

As an effectiveness-implementation hybrid type I, the primary goal of this study is to assess effectiveness, while also collecting data on implementation parameters [5]. In our prior work using a similar treatment with a traumatized, low-resource population, we observed a Cohen’s *d* effect size of 0.79 for depression symptoms [20]. Using the depression Cohen’s *d* would suggest that a sample size of at least 50 is necessary for a two-group design with power of 50 and probability level of 0.05. However, given cultural differences between studies, and that this study requires participants to complete four assessments across 36 weeks, with substantial time investment at each assessment, we have made a conservative sample size estimate, allowing for approximately 20 % general attrition at each assessment point, a sample size of 100 was selected. Given the multiple blood draws required of participants and the evidence suggesting that fear of blood draw can lead to attrition [50], we will further increase our sample size to 200 patients.

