**Methods/Design:**

In this effectiveness-implementation hybrid type I design, 200 HIV+ women with major depressive disorder (MDD) and posttraumatic stress disorder (PTSD) who are receiving care at a Family AIDS Care Education and Services (FACES)-supported clinic in Kisumu, Kenya will be randomized to: (1) interpersonal psychotherapy (IPT) + treatment as usual (TAU) or (2) TAU, both delivered within the HIV clinic. IPT will consist of 12 weekly 60-minute individual IPT sessions, delivered by non-specialists trained to provide IPT. Primary effectiveness outcomes will include MDD and PTSD diagnosis on the Mini International Diagnostic Interview (MINI). Primary implementation outcomes will include treatment cost-benefit, acceptability, appropriateness, feasibility and fidelity of the IPT delivery within an HIV clinic.

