#### Randomization

Blocks of 10–20 participants will be randomized to: (1) IPT + TAU or (2) TAU until reaching the target of 220 participants. The variation in randomization blocks will minimize transparency of assignment and maintain blinding.

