### Statistical analysis

#### Effectiveness

The main analysis will consist of comparing the change from baseline to post-treatment (12 weeks) between the two treatment conditions. The two primary outcome measures of PTSD and MDD diagnosis will be analyzed by estimating and testing a statistical model of each dichotomous measure with a binomial distribution and log link using generalized estimating equations to account for clustering of participants by therapist (therapist effect) and the repeated assessments. Maintenance of gains will be assessed by testing for significant change from 12-week to 24- and 36-week follow-up assessments within each condition using McNemar’s test and repeated measures *t* tests.

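### The stated power does not match the stated sample size (50 participants at d = 0.79 give about 78 to 80% power, not 50%), and the effect size is for a symptom score rather than the two binary primary diagnoses

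*Protocol article*

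**What the plan says.** The Sample size section of the protocol article takes its planning value from the investigators' earlier work with a similar treatment: an "effect size of 0.79 for depression symptoms". From this it states that "a sample size of at least 50 is necessary for a two-group design with power of 50 and probability level of 0.05". It then allows for "approximately 20 % general attrition at each assessment point", after which "a sample size of 100 was selected", and finally doubles that to 200 because repeated blood draws may cause further loss.

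The outcomes to be tested are of another type. The abstract states that "Primary effectiveness outcomes will include MDD and PTSD diagnosis", assessed on the MINI. Under Statistical analysis, Effectiveness, "The two primary outcome measures of PTSD and MDD diagnosis" are to be modelled as dichotomous variables with a binomial distribution and log link, using generalised estimating equations that account for clustering by therapist. The main comparison is the change from baseline to week 12.

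**The concern.** There are two separate problems in one paragraph.

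First, this is the only power figure in the article, and it does not fit the sample size and effect size printed beside it. Taken literally, it says that the trial was planned from a sample with an even chance of missing its target effect.

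Second, the effect size belongs to a continuous depression score. A difference in means on a symptom scale does not by itself fix a difference in the proportion who still meet a diagnosis, and the figure concerns depression only. The paragraph therefore justifies the sample size for an analysis that is not the primary one. A reader cannot learn from it what difference in MDD or PTSD remission the trial was designed to detect.

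**Working it through.** **Inputs from the article.** d = 0.79; "probability level of 0.05"; N = 50; 20% attrition per assessment; 100 after attrition; 200 finally; follow-up assessments at weeks 12, 24 and 36.

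**Assumptions for what is not stated.** Two-sided test, 1:1 allocation, and 50 as a total over both arms. The attrition step supports reading 50 as a total: three post-baseline assessments give 50 / 0.8³ = 97.7, close to the stated 100.

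**1. The stated figure.** For two means, n per arm = 2(z₁₋α/₂ + z_power)² / d².

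- 50% power: 2 × 1.960² / 0.79² = 12.3, so 13 per arm and 26 in total. The noncentral t gives 14 per arm and 28 in total.
- 80% power: 2 × (1.960 + 0.842)² / 0.79² = 25.15, so 26 per arm and 52 in total (50.3 before rounding up). The noncentral t gives 27 per arm and 54 in total.
- Power at 25 per arm: Φ(0.79 × √(25/2) − 1.960) = 79.8%. The noncentral t gives 78.1%.

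Other readings do not rescue 50%. A one-sided test at 25 per arm gives 87.5% (normal) or 86.6% (t). Reading 50 as the number per arm gives 97.7% or 97.4%. A two-sided level of 0.025 at 25 per arm gives 70.9% or 68.4%. The printed N is close only to the N for 80% power.

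**2. The same effect on a binary outcome.** The article gives no remission rates, so TAU remission of 20 to 50% is assumed. With a latent normal variable shifted by 0.79, remission under IPT + TAU is Φ(Φ⁻¹(p) + 0.79). Of 200 randomised, 20% lost by week 12 leaves 160, or 80 per arm. For therapist clustering, 10 women per therapist and an intraclass correlation of 0.05 are assumed. The design effect in the IPT arm is then 1 + 9 × 0.05 = 1.45, and the effective IPT arm is 80 / 1.45 = 55.2. Power is from the two-proportion test with pooled variance under the null, two-sided 0.05, for each outcome separately.

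| TAU remission (assumed) | IPT + TAU remission | Power, 80 per arm | Power with design effect 1.45 |
|---|---|---|---|
| 20% | 48% | 96.8% | 93.2% |
| 30% | 60% | 97.8% | 94.7% |
| 40% | 70% | 97.8% | 94.7% |
| 50% | 79% | 97.1% | 93.4% |

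At the starting figure of 25 per arm, the same conversion gives 55 to 59% power, and 80% power needs 82 to 88 women in total. The starting figure would therefore have been too small for a diagnosis outcome, but it is not the number enrolled.

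**3. Detectable differences at 80 per arm, about 80% power.**

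- No clustering: 30% vs 52% (81%; 51% gives 78%), or 40% vs 62% (80%).
- Design effect 1.45 in the IPT arm: 30% vs 54% (80%), or 40% vs 64% (79%).

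**The case against.** The strongest reply is that the power figure is a one-digit misprint. Read as 80, it fits: the normal formula gives 50.3 in total before rounding, and the step to 100 follows from three rounds of 20% loss. This stands as the likely explanation, and it means that the starting N is roughly right for the effect size used. The printed figure is still wrong and needs correction.

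The second reply is that 50 is only a starting value and the trial enrols 200. This also stands. A reader might infer from the 55 to 59% power at 25 per arm that the trial is too small for its primary outcomes. The documents do not support that, because the enrolled number is four times the starting value and the planned effect keeps a comfortable margin (step 2). Even after three rounds of 20% loss, 200 × 0.8³ = 102 women (51 per arm) would give 86 to 88%, ignoring clustering.

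The third reply is that a condensed article may leave a PTSD calculation and a clustering allowance to the full protocol or analysis plan. That is fair, and their absence is not counted as an error here. What remains is what the article does state: a power figure that fails, and an effect size for a different type of outcome.

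Finally, what a null result excludes will be read from the confidence interval of the estimate, not from the planning paragraph. This limits the harm.

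**Conclusion.** The point holds in two parts. The stated power is wrong for the stated N and effect size: about 78 to 80% rather than 50%, most likely a slip for 80. The effect size is for a continuous depression score, so the justification is not that of the two binary primary outcomes. Neither part depends on an assumed remission rate. The first assumes equal allocation and 50 as a total, and none of the alternative readings tried gives 50%.

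Inadequate power is not shown. The 97 to 98% (93 to 95% with clustering) rests on the assumed TAU remission range, the latent-normal conversion, 20% loss by week 12, and the assumed therapist caseload and intraclass correlation. For PTSD it also borrows an effect size that the article gives only for depression. Smaller differences than those in step 3 would have less than 80% power, and the article does not let a reader see where that limit lies. The calculation uses 200 randomised, as in the Sample size section; the Randomization section gives 220, which would only raise the power. Severity: should be fixed, not critical.

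**What to change.** Rewrite the Sample size paragraph and leave enrolment as planned.

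- Check the original calculation and correct the power figure (probably 80). State whether the test is two-sided and that 50 is a total.
- Restate the justification on the week-12 diagnoses, at about 80 evaluable women per arm. Give the assumed TAU remission range and the difference detectable with 80% power for MDD and for PTSD. For example: about 30% vs 52% or 40% vs 62% without clustering, and about 30% vs 54% or 40% vs 64% with a therapist design effect of 1.45.
- Label the remission rates, the caseload and the intraclass correlation as assumptions, and replace them with the team's own figures where these exist.

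The cost is one rewritten paragraph, with no extra participants and no change to the analysis. The downside is that the stated power basis becomes slightly less favourable than a calculation on a symptom score suggests.

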### Data management

Data collection will be done with paper and tablets. Informed consent will be in paper format, allowing participants to either sign or use a thumbprint to acknowledge receipt of information. Eligibility screening and measures will be collected on Android tablets using an electronic data capture, CommCare Open Data Kit (ODK). ODK is widely used in low- resources setting, is user-friendly and allows users to input data offline, then upload through a secure server. In addition, all screening and therapy sessions will be audiotaped and uploading into REDCap. REDCap is a secure, web-based application designed to support data capture for research studies, providing: (1) an intuitive interface for validated data entry; (2) audit trails for tracking data manipulation and export procedures; (3) automated export procedures for seamless data downloads to common statistical packages; and (4) procedures for importing data from external sources. Audio sessions will be randomly selected for review by an independent rater for external validity.

### Statistical analysis

#### Effectiveness

The main analysis will consist of comparing the change from baseline to post-treatment (12 weeks) between the two treatment conditions. The two primary outcome measures of PTSD and MDD diagnosis will be analyzed by estimating and testing a statistical model of each dichotomous measure with a binomial distribution and log link using generalized estimating equations to account for clustering of participants by therapist (therapist effect) and the repeated assessments. Maintenance of gains will be assessed by testing for significant change from 12-week to 24- and 36-week follow-up assessments within each condition using McNemar’s test and repeated measures *t* tests.

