## Design/Methods

### Aims

We will conduct an effectiveness-implementation hybrid type I study of IPT + treatment as usual (TAU) versus TAU alone for major depressive disorder (MDD) and posttraumatic stress disorder (PTSD) among HIV+ GBV+ women receiving HIV care at FACES in Kisumu. IPT will be offered to the TAU group after the conclusion of the 12-week IPT. We will assess the effectiveness of IPT + TAU versus TAU alone for reduction of depression and PTSD symptoms, HIV viral load and improvement of ART adherence and neurocognitive functioning. We will also assess implementation parameters, including cost-benefit analyses of delivering IPT integrated within HIV clinics using non-specialist providers, fidelity and adoption of the intervention. We hypothesize that IPT + TAU will be more effective than TAU alone for remission of MDD and PTSD and that implementation analyses will show that it is delivered with high fidelity and adoption and that the benefits outweigh the costs.

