#### Inclusion criteria

Participants will be HIV+ women who receive care from FACES-Kisumu, are at least 18 years old, diagnosed with MDD and PTSD secondary to GBV on the Mini International Neuropsychiatric Interview (MINI 5.0), have the ability to attend once a week therapy sessions for 12 weeks and provide written informed consent.

Of note, while the sample size and analyses required to complete a psychometric evaluation of all measures used in our protocol is not within the scope of this study, the MDD and PTSD modules of the widely used, internationally validated MINI [22] were adapted for the local culture and translated into the local languages, Dholuo and Kiswahili, using a standardized process of separate forward and backward translation, with an iterative team approach to resolve discrepancies [23]. This strategy is now widely practiced in the field of global mental health, where separate validation studies for each distinct population have not driven changes in diagnosis or treatment needs, as it was once thought they might [24]. All measures will be read to participants secondary to local literacy rates.

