### Assessments

All study participants in both study arms will be assessed with the same instruments at baseline, 12 weeks, 24 weeks and 36 weeks, with the exception of the trauma history questionnaire, which will only be administered at baseline.

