#### Effectiveness outcomes

##### Clinical measures

Given the strong association between substance use and trauma-related disorders (“dual-diagnosis”) [29], as well as the impact of the former on overall health, we will measure changes in alcohol and drug use as a secondary outcome for this mental health treatment study of HIV+ GBV+ women. We will use two well-established measures, the Alcohol Use Disorders Identification Test (AUDIT)) [30] and the Drug Abuse Screening Test (DAST) [31]. The AUDIT is a simple 10-question test developed by the World Health Organization to determine if a person’s alcohol consumption over the past 12 months may be harmful. The DAST is a 10-item brief screening tool that assesses drug use, not including alcohol or tobacco use, in the past 12 months.

The Beck Depression Scale (BDI) [32]. The BDI was developed in 1961 and is a 21-item rating inventory that measures characteristic attitudes and symptoms of depression. The BDI is a widely used measure of depression symptoms.

The Conflict Tactics Scale (CTS2) [33]. The CTS was created to measure psychological and physical attacks on a partner in a marital, cohabiting, or dating relationship; and also use of negotiation. The CTS2 is a 39-item revised version of the CTS with expanded evaluation of validity, reliability and specificity.

The Mini International Diagnostic Interview (MINI 5.0) [22]. The MINI is a short, structured diagnostic interview developed in 1990 by psychiatrists and clinicians in the United States and Europe for *Diagnostic and Statistical Manual of Mental Disorders, fourth edition* (DSM-IV) and *International Classification of diseases, 10th edition* (ICD-10) psychiatric disorders. The MINI has multiple modules. This study uses the depression and PTSD modules. The MINI can be administered by lay personnel and takes an average of 15 minutes to complete.

The Posttraumatic Stress Disorder Checklist-Civilian (PCL-C) [34]. For this study, we used the PCL which is a 17-item measure of DSM-IV symptoms of PTSD.

The Social Adjustment Scale (SAS) [35]. The SAS is a 54-item scale that assesses behavioral and emotional social adjustment across six major areas: work, leisure, extended family, primary relationship, parental and family unit.

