## Discussion

While the treatment gap for mental health care has been recognized for nearly 20 years, with a few exceptions [51] the majority of studies addressing this gap have used efficacy designs without the benefit of implementation science. This trial will leverage newly defined effectiveness-implementation hybrid designs [5] to gather data on treatment implementation within an HIV care clinic, while testing the effectiveness of an evidence-based treatment for use with a large underserved population (HIV+ GBV+ women) in Kenya. This trial is likely to yield findings that will be generalizable beyond the study population and, if effective, could be scaled up for treatment of HIV+ women in Kenyan HIV clinics and perhaps other countries in sub-Saharan Africa facing a similar HIV-GBV syndemic among women.

Despite awareness of the relationships between GBV, mental disorders and HIV outcomes, this is the first study of which we are aware that intervenes on mental disorders among HIV+ GBV+ women and also collects data on HIV and neurocognitive outcomes. We expect these secondary outcomes to inform women’s HIV care in the region and to shed light on the mechanisms of ART deficits and re-victimization commonly observed among HIV+ GBV+ women.

We recognize a number of limitations in this study. First, generalizability may be limited given that this is a single center study; future multi-center studies will be needed. Another limitation of this study is the TAU control. While TAU includes access to mental health care services, data bearing on the particular efficacy of IPT would be stronger if an active control with similar meeting schedule was included (e.g., weekly, individual supportive therapy). However, given that this study is not intended to test the efficacy of IPT, which has already been established across diverse populations and disorders, but rather to evaluate its effectiveness with a more general and diverse population (HIV+ GBV+ women with MDD and/or PTSD) when implemented by non-specialists within an HIV clinic, we have elected to focus resources on data that will inform scale-up of care.

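### The between-arm effectiveness contrast is worded as change from baseline to week 12, with no baseline adjustment; for the continuous secondary outcomes, adjusting for the baseline value is never less precise and costs nothing

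*Protocol article*

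**What the plan says.** Statistical analysis, Effectiveness, opens with the contrast: "The main analysis will consist of comparing the change from baseline to post-treatment (12 weeks) between the two treatment conditions". It then names the two diagnoses as the primary outcomes and gives their model: "a statistical model of each dichotomous measure with a binomial distribution and log link using generalized estimating equations". The only other tests are for maintenance of gains after week 12. They are run "within each condition using McNemar’s test and repeated measures" t tests, so they are not comparisons between arms. Their presence does show that the section has continuous scores in view as well as diagnoses.

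The Aims promise a comparison of the arms "for reduction of depression and PTSD symptoms, HIV viral load and improvement of ART adherence and neurocognitive functioning". Clinical measures lists the symptom and functioning scales; of one it says: "The BDI is a widely used measure of depression symptoms". Under Assessments, both arms are "assessed with the same instruments at baseline, 12 weeks, 24 weeks and 36 weeks", with the trauma history as the one exception. Every continuous outcome therefore has a baseline value. No between-arm model is named for any of them.

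The inclusion criteria require women "diagnosed with MDD and PTSD secondary to GBV on the Mini International Neuropsychiatric Interview (MINI 5.0". The Discussion describes the population differently, as "HIV+ GBV+ women with MDD and/or PTSD".

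**The concern.** Change from baseline is the only between-arm rule that the section states, so the natural reading is that it also governs the symptom, functioning, adherence and neurocognitive scores. Taken literally, each woman's baseline score would be subtracted from her week-12 score and the mean differences compared between arms.

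Subtraction forces the slope of week 12 on baseline to be 1. When the true slope is lower, which is usual, two things follow. Baseline noise is added to the outcome and widens the confidence interval. An arm that happens to start worse also appears to improve more. Using the baseline value as a covariate estimates the slope instead and avoids both. What is at stake is precision on the secondary outcomes, including the symptom reduction named in the Aims.

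**Working it through.** **Inputs.** From Sample size: d = 0.79 for depression symptoms, about 20% attrition per assessment, 200 women. That leaves 200 × 0.8 = 160 at week 12, or 80 per arm. (Randomization gives a target of 220; the variance ratios below do not depend on N.) The article gives neither the baseline to week-12 correlation r nor any SD. I take r = 0.3, 0.5 and 0.7 as an assumed range, and write k for week-12 SD divided by baseline SD.

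**The plan's own figure.** The article states no precision figure for the continuous outcomes. Its only related figure is the minimum of 50 women for d = 0.79. Two-sided alpha 0.05 and 80% power give 2 × (1.96 + 0.842)² / 0.79² = 25.2, so 26 per arm or 52 in total. The minimum thus fits 80% power; the printed power of 50 would need only 13 per arm. That is a separate matter and does not bear on this point.

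**Step 1: primary outcomes.** If every woman has both diagnoses at baseline, change in diagnosis equals week-12 status minus a constant. The arm difference and its standard error are identical either way, and the loss is 0%.

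**Step 2: direction for continuous outcomes.** In units of the baseline variance, per woman and in large samples:

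- change score: 1 + k² − 2rk
- baseline-adjusted week-12 value: k²(1 − r²)
- difference: 1 − 2rk + r²k² = (1 − rk)², which is never negative.

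The two are equal only when rk = 1.

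**Step 3: size with equal SDs (k = 1).** The ratio of adjusted to change-score variance is (1 − r²) / (2(1 − r)) = (1 + r)/2, so the loss is (1 − r)/2. The detectable difference at 80% power is 2.802 × √((2/80)v), with v = 2(1 − r) for change and v = 1 − r² for adjusted.

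| r | Variance loss | CI narrower with adjustment | Detectable difference, change → adjusted (SD) |
|---|---|---|---|
| 0.3 | 35% | 19% | 0.52 → 0.42 |
| 0.5 | 25% | 13% | 0.44 → 0.38 |
| 0.7 | 15% | 8% | 0.34 → 0.32 |

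**Step 4: unequal SDs.** Entry on diagnosis may narrow the baseline spread of BDI and PCL-C, which makes k greater than 1. The loss is 1 − k²(1 − r²)/(1 + k² − 2rk). At k = 1.5:

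- r = 0.3: 1 − 2.0475/2.35 = 13%
- r = 0.5: 1 − 1.6875/1.75 = 4%
- r = 0.7: 1 − 1.1475/1.15 = 0.2%

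The correlation below which a change score is noisier than ignoring baseline altogether is 1/(2k): 0.5 with equal SDs, 0.33 at k = 1.5.

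**Step 5: chance imbalance.** Given a baseline difference D between arms, the change-score estimate is shifted by −(1 − rk)D. With 80 per arm, one standard error of D is √(2/80) = 0.158 SD. At k = 1 the shift is then 0.7 × 0.158 = 0.11 SD at r = 0.3 and 0.3 × 0.158 = 0.05 SD at r = 0.7.

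**Step 6: power, 80 per arm, k = 1.** At d = 0.79 and r = 0.3, power is 98.8% (change) against 99.9% (adjusted); at r = 0.5 or more it is practically 100% both ways. At an assumed d of 0.4 it is 57% against 76% (r = 0.3), 72% against 83% (0.5) and 90% against 94% (0.7).

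**The case against.** The strongest reply is that the article does not specify the analysis being criticised. The contrast sentence introduces the main analysis, the next sentence ties it to the two diagnoses, and no between-arm model is given for any continuous outcome. A journal article may leave such models to a fuller plan. This stands in part: applying the change-score rule to the continuous outcomes is an inference. It is the natural one, because the section states no other rule and plainly covers continuous scores.

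Second, comparing change does not have to mean an unadjusted change score. A model for change with baseline as covariate gives the same treatment effect as a model for the week-12 value with that covariate, and a repeated-measures model with a common baseline mean is about as efficient. This also stands. The wording rules none of these out, but it commits to none either.

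A reader might go further and infer any of the following, which the article does not support:

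- **That the primary analysis loses precision.** It does not, provided both diagnoses are required at entry. The Discussion's and/or description conflicts with the inclusion criteria and needs reconciling, because this conclusion rests on a constant baseline.
- **That a loss of 15 to 35% is a property of this trial.** It is (1 − r)/2 at assumed r of 0.7 and 0.3 with equal SDs, and it measures variance, not interval width. Arguing that entry on diagnosis restricts the baseline range while keeping equal SDs pulls in two directions, as step 4 shows.
- **That change scores are biased because the women were selected as cases.** Randomisation keeps the comparison unbiased on average. The shift in step 5 comes from chance imbalance whenever rk differs from 1, and selection by diagnosis applies to both arms alike.
- **That the trial is underpowered as a result.** At the planning effect it is not.

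**Conclusion.** The point holds as a low-severity efficiency improvement for the continuous secondary outcomes (BDI, PCL-C, SAS, WHODAS, WHOQOL-BREF, neurocognition, self-reported adherence), not as an error in the primary analysis. If the stated contrast is applied to them unadjusted, it can at best equal baseline adjustment, and it over-corrects chance imbalance whenever r × SD12/SD0 is below 1.

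The direction needs no assumption about r or the SDs. The size does, and it runs from a third of the variance to almost nothing over the values shown. The smaller losses are most plausible for BDI and PCL-C, whose baseline spread may be narrowed by entry on diagnosis; that argument is weaker for scales on which women were not selected. The practical benefit is narrower intervals, and better power if the true effect is well below 0.79. Sample size itself cites cultural differences between studies as a reason for caution about carrying that effect over.

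**What to change.** Add one sentence to Statistical analysis, Effectiveness: each continuous effectiveness outcome is compared between arms at week 12 with the week-12 value as response and the same measure's baseline value as covariate, by ANCOVA or an equivalent baseline-adjusted or baseline-constrained mixed model or GEE. Report mean change from baseline descriptively. If a fuller plan already says this, align the article's wording with it.

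Separately, reconcile the Discussion's description of the population with the inclusion criteria.

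The cost is one sentence of analysis wording. The baseline values are already scheduled, so no new data and no further participants are needed.

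### Maintenance of gains is assessed with a within-arm test of no change, which cannot show that any worsening was small

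*Protocol article*

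**What the plan says.** Under Statistical analysis, Effectiveness, the main analysis is the between-arm comparison from baseline to week 12. "The two primary outcome measures of PTSD and MDD diagnosis" are modelled there with generalized estimating equations. The later visits are handled in one sentence: "Maintenance of gains will be assessed by testing for significant change" "from 12-week to 24- and 36-week follow-up assessments within each condition". The tests named are McNemar's for the diagnoses and repeated measures t tests, presumably for the scores.

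No tolerable loss, margin or interval rule is attached to this analysis anywhere in the article. By contrast, the paragraph on feasibility and fidelity measures prescribes 95% confidence intervals compared with benchmarks fixed in advance.

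Three other places bear on the point:
- Sample size arrives at 200 women, "allowing for approximately 20 % general attrition at each assessment point".
- Feasibility (under Statistical analysis) sets the attrition benchmark at fewer than 50 women.
- Study design and Treatment as usual offer IPT to the TAU arm once the week-12 assessment is done.

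**The concern.** Maintenance is a claim that little or no worsening occurred. Both named tests take no change as the null hypothesis. The only result of such a test that could be put forward for maintenance is therefore a failure to reject, and that excludes no amount of relapse. Three consequences follow:

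- **Attrition works in favour of the claim.** The fewer women who return, the less often the test reaches significance. Complete data would not remove the fault, only reduce it.
- **A significant result is ambiguous.** It may reflect further improvement, which is no evidence against maintenance.
- **McNemar's test sees only the net shift.** Relapses and late remissions cancel.

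At stake is a statement about durability at weeks 24 and 36. The trial could describe gains as held while its data remain compatible with a sizeable return of MDD or PTSD.

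**Working it through.** **The plan's own figure.** There is none for the maintenance analysis. The only calculation is for the two-group comparison: with an "effect size of 0.79 for depression symptoms", "a sample size of at least 50 is necessary" "for a two-group design with power of 50 and probability level of 0.05". Using n per arm = 2 × ((z₀.₉₇₅ + z_power)/d)²:
- Power 0.50: 2 × (1.96/0.79)² = 12.3, so 13 per arm and 26 in total (28 by the t test). This is not 50.
- Power 0.80: 2 × (2.80/0.79)² = 25.2, so 26 per arm and 52 in total (54 by the t test).

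Fifty women give about 80% power, so the printed power is probably a misprint. That is a separate matter. What counts here is that the trial was not sized for relapse.

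**Women available for the paired tests.** Allocation of 1:1 and equal loss in both arms are assumed.
- Attrition benchmark: 200 − 50 = 150, so about 75 per arm.
- Planned loss compounded over three visits: 100 × 0.8 = 80, × 0.8 = 64, × 0.8 = 51 per arm at weeks 12, 24 and 36. Compounding fits the article's step from 50 to 100 women, since 50/0.8³ = 98.

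**Chance of missing a real loss.** The article gives no relapse or late-remission rates, so three assumed pairs are shown, each with a true net loss of 10 points in the IPT + TAU arm. Let r be the relapse proportion and m the late-remission proportion. The number of discordant pairs D is binomial(n, r + m). Given D, the number of relapses is binomial(D, r/(r + m)). Power is the probability of rejection at two-sided 0.05, summed over D. The entries are 1 − power, with the asymptotic test first and the exact test second.

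| Relapse / late remission | n = 100 | n = 75 | n = 64 | n = 51 |
|---|---|---|---|---|
| 15% / 5% | 36–46% | 50–59% | 58–67% | 66–75% |
| 20% / 10% | 54–63% | 63–72% | 68–76% | 75–82% |
| 10% / 0% | 1–6% | 5–23% | 11–37% | 24–60% |

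Every row has the same net loss. The miss rate depends strongly on how many women change in each direction, and within each row it rises as n falls.

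**What one such result would look like.** Take the first scenario at 75 women: 15% and 5% of 75 round to 11 relapses and 4 late remissions.
- Net loss: 7/75 = 9.3 points.
- McNemar: 7²/15 = 3.27, below 3.84. Exact p = 2 × 1941/32768 = 0.12.
- Interval: SE = √((15/75 − (7/75)²)/75) = 0.0505, so 9.3 ± 9.9 points, or −0.6 to 19.2.

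The test says no significant change, while the data are compatible with a loss of 19 points.

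**Interval half-width.** 1.96 × √((r + m − (r − m)²)/n):
- n = 75: 9.9 points (15%/5%), 12.2 points (20%/10%).
- n = 51: 12.0 points (15%/5%), 14.8 points (20%/10%).
- With 10%/0% it is narrower: 1.96 × √(0.09/75) = 6.8 and 1.96 × √(0.09/51) = 8.2 points.

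**The case against.** The strongest reply is that the article names tests but does not state the faulty conclusion. A reader might infer that the plan commits itself to reporting non-significance as gains held. It does not say so, and presenting the test beside the observed relapse proportion would be compatible with the sentence. That stands. What remains is that the test is the only criterion given, and it cannot answer the question it is assigned.

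A second reply is that margins and interval rules belong in an analysis plan that is not shown. Their absence alone would indeed be no finding. The point here is the method that the article does state.

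Third, the size depends on chosen inputs. A reader might take the figures at 51 women, with a 10-point loss missed in two thirds or more of trials, as the expected performance. The documents do not support that. They give no relapse rates, the 10%/0% case does far better, and about 75 per arm remain if the attrition benchmark is met.

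Fourth, a reader might apply the relapse scenario to both arms. It does not fit the TAU arm, where change from week 12 spans the period in which IPT is offered and improvement is to be expected.

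Finally, the analysis is secondary. The stated hypotheses concern remission under IPT + TAU against TAU, fidelity, adoption and cost, and none of them concerns maintenance.

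**Conclusion.** The point holds as a fault in the stated method of a secondary analysis. A within-arm test of no change cannot establish maintenance, whatever the sample size, and attrition makes the favourable-looking result more likely. For an assumed 10-point net loss in the IPT + TAU arm, the miss rate at about 75 women runs from 5–23% to 63–72% over the three scenarios. At 51 women it runs from 24–60% to 75–82%. These ranges rest on the assumed relapse and late-remission rates, 1:1 allocation and equal loss by arm. The logical fault rests on none of them. The primary between-arm comparison at week 12 is not affected.

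**What to change.** Replace the sentence on maintenance with an estimate and a rule:

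- Report the paired change in each diagnosis, and in BDI and PCL-C scores, after the end of IPT with a 95% confidence interval. For the IPT + TAU arm the reference is week 12.
- Base any statement on maintenance on the worsening-side limit, judged against a largest tolerable loss that the investigators fix beforehand. The documents give no basis for a particular value, and none is proposed here.
- If the interval includes a larger loss, report that maintenance was not shown. Do not read non-significance as maintenance, or significant improvement as its failure.
- For the TAU arm, do not label change from week 12 as maintenance.

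The change is to analysis wording only and needs no new data. The cost is a harder claim: with half-widths of about 10–12 points at 75 women and 12–15 points at 51 in the two scenarios with late remission, the trial may be unable to exclude a moderate loss. That limit already exists, and the interval makes it visible.
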